#### Inclusion criteria

Patients meeting all of the following criteria will be enrolled in the study.

No gender restriction, from 18 to 70 years old;Meeting the International Classification of Sleep Disorders-Third Edition (ICSD-3) diagnostic criteria for insomnia;8 ≤ Insomnia Severity Index (ISI) score ≤ 22;Meeting the Chinese Guidelines for the Prevention and Treatment of Hypertension (2018 Revised Edition) diagnostic criteria of primary hypertension (35);The cardiovascular risk stratification is low to medium risk (35), the blood pressure control is relatively stable, and the types of hypertension drugs taken are Calcium Channel Clocker (CCB)+ Angiotensin-Converting Enzyme Inhibitors (ACEI)/Angiotensin Receptor Blockers (ARB), but no more than two types;Voluntarily participate in this trial and sign the informed consent.

#### Exclusion criteria

Patients meeting any of the following criteria will be excluded from the study:

Patients with serious physical diseases, such as heart failure, myocardial infarction, cerebral infarction, malignant tumor, etc.;Hamilton Anxiety Scale (HAMA) score ≥2 or Hamilton Depression Rating Scale (HAMD) score ≥18;Caffeine, alcohol or psychotropic substances dependence;Other types of sleep disorders such as sleep apnea and restless legs syndrome;Night shift workers;Stop insomnia-related interventions (including traditional Chinese medicine, acupuncture, massage, and western medicine) ≤ 2 weeks;Change of antihypertensive plan within the last 1 month;Pregnant and lactating women;Patients are participating in other trials.

#### Drop-out criteria

Patients who refused to cooperate with the test and diagnostic errors after enrollment were considered as excluded cases;During the study period, patients dropped out, did not complete the whole course of treatment, and poor compliance were considered as abscission cases.Patients who could not tolerate acupuncture, had serious adverse events during treatment, or had serious complications caused by other diseases would terminate the trial.

### Intervention

#### Initial therapy

Both groups will obtain unified sleep hygiene education and hypertension health education by means of pushing articles through the WeChat platform. All patients will be allowed to routinely take their hypertension medication.

#### The treatment group

The treatment group will be given acupuncture treatment at DU20 (Baihui), EX-HN3 (Yintang), HT7 (Shenmen), SP6 (Sanyinjiao), LR3 (Taichong), and KI3 (Taixi), and the above acupoints will be strictly in accordance with *National Standard of China: Meridian Points* (GB12346–90). The subjects will be placed in the supine position and the physician will select 0.30 mm × 40 mm disposable sterile acupuncture needles (Suzhou Medical Products Factory Co., Ltd.). The angle and depth of needling will be based on the standard of each acupoint. The acupuncture needles will be inserted into the acupoints and lifted and twisted to achieve the state of *deqi*. The low-frequency pulse electro-acupuncture therapeutic apparatus (XS-998B04; Nanjing Xiaosong Medical Instrument Research Institute Co., Ltd., Nanjing, China) will be used to connect the needle handles at DU20 and EX-HN3, and the electric stimulation will be applied with a 2 Hz frequency and continuous wave type at an intensity that the subject can notice but feel comfortable with. After continuous stimulation for 30 min, the points will be compressed with a sterilized cotton ball to prevent bleeding upon needles withdrawal. Participants will accept acupuncture treatment three times a week for 4 weeks (12 sessions totally). All acupuncture procedures will be performed by the same acupuncturist.

#### The control group

The sham-acupuncture method of shallow acupuncture at non-disease-related points will be applied to the control group. LI10 (Shousanli), LI14 (Binao), ST32 (Futu), BL58 (Feiyang) acupoints will be selected, and the acupoints will be strictly in accordance with National Standard of China: Meridian Points (GB12346–90). The subjects will be placed in the supine position and the physician will select 0.30 mm × 25 mm disposable sterile acupuncture needles (Suzhou Medical Products Factory Co., Ltd.). After routine disinfection, the needles will be inserted only for 1–2 mm and avoid manual stimulation and the sensation of *deqi* in order to minimize placebo effect. The low-frequency pulse electroacupuncture therapeutic apparatus (same as the treatment group) will be placed beside the patient, and the needle handle will be connected at LI10 and ST32 acupoints on one side, the apparatus will turned on, but the stimulation intensity button will not turned on, and the needle will removed after 30 min. Participants will accept sham-acupuncture treatment three times a week for 4 weeks (12 sessions totally). At the end of the study, the same treatment as the treatment group was received. All acupuncture procedures will be performed by the same acupuncturist.

### Outcome measures

#### Primary outcome measures

PPSG is one of the sleep monitoring methods with the advantages of supporting home environment monitoring and avoiding the influence of the first night effect, which can be used for objective diagnosis of insomnia, treatment evaluation and differential diagnosis of sleep diseases. In this study, Anbaolan wearable portable sleep recorder [202070644; Embla (Beijing) Medical Equipment Co., Ltd., Beijing, China] was applied to sleep monitoring. The device records electroencephalogram (EEG), electrooculogram (EOG) and electromyogram (EMG) signals through a set of head-mounted sensors, monitors blood oxygen with finger pulse oxygen, and uses AI intelligent algorithms to evaluate sleep structure in detail, including wakefulness (W) and rapid eye movement sleep (REM) sleep period), N1 stage sleep, N2 stage sleep, N3 stage sleep, and then the sleep quality evaluation indicators such as sleep efficiency (SE), sleep awakening times (SA) and total sleep time (TST) can be obtained, which can provide real-time and objective sleep evaluation indices for individuals. Sleep parameters of PPSG will be collected one night and evaluated before treatment and after 4 weeks of treatment.

#### Secondary outcome measures

Pittsburgh Sleep Quality Index (PSQI) is a questionnaire to assess the sleep quality of individuals. The total score of PSQI is 0–21 and the score is inversely proportional to the sleep quality, namely, the higher the PSQI score, the worse the sleep quality. PSQI > 7 was used as the reference threshold for judging sleep quality problems. PSQI will be evaluated before treatment and after 4 weeks of treatment.

ISI questionnaire is designed to evaluate severity of insomnia through 7 self-assessment items corresponding to the symptoms of insomnia. In the present study, 8 ≤ ISI ≤ 22 will be taken as the inclusion criterion. ISI score will be measured before treatment and after 4 weeks of treatment.

HAMA is created to evaluate patients' anxiety symptoms. There are 14 items scored by 5-point scale from 0 to 4. According to the data provided by the China Scale Collaboration Group, a total score <7 indicates no anxiety symptoms, a score of 7–13 indicates possible anxiety, a score of 14–20 indicates definite anxiety, a score of 21–28 indicates definite anxiety, and a total score ≥29 indicates severe anxiety. The depressive symptoms will be assessed using Hamilton Depression Rating Scale (HAMD) drawn with 24 items. The scoring criteria are as follows: a total score of <8 indicates normal, a total score of 8 to 17 indicates possible depression, a total score of 18–24 indicates depression, and a total score of >24 indicates severe depression. The above two scales are other-report questionnaires, which will be evaluated before enrollment to exclude individual with severe mental illness. HAMA score ≥29 or HAMD score ≥18 will be considered as one of the exclusion criteria in this study.

Sleep diary, a standard subjective assessment tool for insomnia, is used to observe the severity of insomnia in patients and monitor sleep improvement during treatment, which can capture sleep information such as the bedtime at the previous night, sleep latency, waking time in the morning, get-up time, the number and duration of wake times after sleep onset, total sleep time, in-bed time, and the use of sedative hypnotics. At the same time, blood pressure records will be added to the back of the sleep diary. The blood pressure monitoring method in this study adopts home blood pressure monitoring. Participants are required to bring their own Omron electronic blood pressure monitors at home, and the patients are instructed to record the systolic and diastolic blood pressure at 8 a.m. and 20 p.m. per day. During this study, participants will be allowed to use sedative-hypnotic drugs, but it is necessary to emphasize the recording of patients' daily sleeping pill use through a sleep diary, and the use of sleeping pills throughout the trial period will evaluated by calculating a weekly sleeping pill score as part of the efficacy analysis. The participants self-reported sleep-blood pressure diary will be collected from 1 week before treatment to the end of the trial.

Portable dynamic ECG recorder can collect and analyze total heart rate, mean heart rate, minimum heart rate, maximum heart rate, maximum RR interval, suprventricular beats, ventricular beats, heart rate variability and other parameters. In this study, the HRV indicators of participants will be collected by using the single-lead portable ECG recorder (JiangSu Registration No. 20182210915) produced by Nanjing Fengsheng Yongkang Software Technology Co., Ltd. The study mainly collected the heart rate of patients during sleep and analyzed the HRV. HRV usually denoted by the variance in the inter-beat interval or distance between two consecutive R waves, referred to as the R–R interval. We mainly analyzed the time-domain parameters of HRV, including the standard deviation of mean value between RR intervals (SDNN), root mean deviation of difference between adjacent RR intervals (RMSSD) and mean deviation of RR intervals (SDANN), and the percentage of the difference between adjacent NN >50 ms in the total number of sinus heartbeats (PNN50). The monitoring time is the same as PPSG. The two groups of patients were evaluated before treatment and at the end of treatment.

### Sample size

The calculation of sample size will be based on the change of ISI scores. According to the results of existing published literature (36), the overall standard deviation of ISI scores in patients of hypertension with insomnia was 5.5, ISI scores decreased by 3.3 after treatment, α = 0.05, β = 0.10, and *N* ≈ 24 cases were calculated. Considering the factors of contamination, non-compliance and shedding during the test, the shedding rate was determined to be 20%, so there were 30 cases in the treatment group and 30 cases in the control group. For comprehensive consideration, a total of 60 samples will be required for this study.

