**Methods:**

A single-center, subject-and-assessor-blind, randomized, sham-controlled trial has been designed for a study to be conducted in Jiangsu Province Hospital of Chinese Medicine. Sixty eligible patients will be randomly assigned to the treatment group and the control group in a 1:1 ratio. The treatment group will receive acupuncture treatment, while the control group will receive sham acupuncture treatment. Both groups will be treated three times per week for 4 weeks. Data will be collected at baseline and after 4 weeks of treatment and analyzed by using SPSS 25.0. The primary outcome measures are sleep parameters of portable polysomnography before and after treatment. Secondary outcomes are Pittsburgh Sleep Quality Index, Insomnia Severity Index, home blood pressure, and heart rate variability.

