Acupuncture, as the most representative non-pharmaceutical therapy of TCM, has been widely applied to treat a variety of diseases ascribe to its unique advantages such as simplicity, safety, and no side effects. Now, acupuncture treatment of insomnia has been recommended by the “*Guidelines for the Diagnosis and Treatment of Insomnia in China*” (2). The meta-analysis (20) has revealed that acupuncture is effective in insomnia, and it is not a placebo effect. A small number of domestic studies have shown that acupuncture can improve the sleep quality of patients with hypertensive stroke, and the improvement of sleep quality can assist in regulating the early morning blood pressure of patients (21, 22). However, there are completely few clinical studies on the intervention of acupuncture on hypertension with insomnia, and it is still inconclusive whether acupuncture can improve insomnia and regulate blood pressure at the same time. In addition, the current researches have problems such as sleep outcome indicators mainly relying on scales and lack of objective evaluation. However, polysomnography (PSG), a “gold standard” assessment tool for the diagnosis of sleep disorders, is cumbersome to operate due to its large size and multiple leads, which not only affects the natural sleep state and fails to describe the real sleep state, but also lacks long-term monitoring conditions, causing it inconvenient for clinical practice (23). Compared with PSG, portable polysomnography (PPSG) has the superiorities of simple operation and home monitoring, small first-night effect, strong endurance and so on. Artificial Intelligence (AI) algorithm was used to evaluate sleep structure and sleep quality in detail, analyze and mark manual/automatic sleep-related events, judge and count micro-awakenings, and quickly identify sleep characteristic waveform, with an accuracy of 95% (24). The validity of PPSG in assessing Sleep has been recognized in several researches and meets the standards of America Academy of Sleep Medicine (AASM) (25).

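### The sample size rests on the ISI, a secondary outcome, so the stated 90% power does not apply to the polysomnography primary outcome

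*Protocol article*

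**What the plan says.** The abstract fixes the hierarchy of outcomes. On the primary it says: "The primary outcome measures are sleep parameters of portable polysomnography before and after treatment". On the rest it says: "Secondary outcomes are Pittsburgh Sleep Quality Index, Insomnia Severity Index, home blood pressure, and heart rate variability". The section on primary outcome measures describes the PPSG device, the sleep stages it scores, and summary indices: "sleep efficiency (SE), sleep awakening times (SA) and total sleep time (TST) can be obtained". It names no single parameter as the primary one and gives no expected difference or SD for any of them. Recording is for one night before treatment and one night after 4 weeks.

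The Sample size section then states that "The calculation of sample size will be based on the change of ISI scores". Its inputs are that "the overall standard deviation of ISI scores in patients of hypertension with insomnia was 5.5", that "ISI scores decreased by 3.3 after treatment", and "α = 0.05, β = 0.10". From these it obtains about 24 cases. Allowing 20% for drop-out, it sets 30 per group and 60 in total.

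The Statistical analysis section compares the groups by t-test or rank sum test and applies a significance threshold of 0.05 throughout.

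**The concern.** The outcome that the trial is meant to answer and the outcome that sets its size are different. A reader who sees β = 0.10 will take it as the power of the primary comparison. Nothing in the article supports that: it gives no PPSG effect, no PPSG SD, and no argument linking a change in ISI to a change in any PPSG parameter. The Introduction also criticises existing research for "sleep outcome indicators mainly relying on scales and lack of objective evaluation", which makes an unexplained reliance on a scale for sizing harder to defend.

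What is at stake is the reading of a null result. If the PPSG comparison is not significant, a reader relying on the stated power would conclude that a worthwhile effect has been ruled out with 90% assurance. The document does not support that conclusion.

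**Working it through.** **Inputs.** All from the Sample size section: SD 5.5 and decrease 3.3 (both ISI points), α = 0.05 with sidedness not stated, β = 0.10, about 24 cases before drop-out, 20% drop-out, 30 per group. The standardised ISI effect is 3.3 / 5.5 = 0.60.

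**1. Reproducing the plan's figure.**
- Drop-out step: 24 / (1 − 0.20) = 30. This reproduces.
- Two-group formula per arm, n = 2 × ((z_α + z_β) / 0.60)²:
  - two-sided: 2 × ((1.960 + 1.282) / 0.60)² = 58.4, so 59
  - one-sided: 2 × ((1.645 + 1.282) / 0.60)² = 47.6, so 48
- Single-group (before–after) one-sided formula: ((1.645 + 1.282) / 0.60)² = 23.8, so 24. The two-sided version gives 29.2.

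The stated 24, used per group, matches the single-group one-sided formula. It does not match a comparison of two groups. (It also appears if the one-sided 48 per arm is misread as a total.)

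**2. What the planned size can detect on a PPSG parameter.** Because no PPSG difference or SD is given, no single power figure can be computed. The detectable between-group effect in SD units can be. For a two-sample t-test, two-sided 0.05, one unadjusted test (noncentral t):

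| Evaluable per arm | 80% power | 90% power |
|---|---|---|
| 24 | 0.83 SD | 0.96 SD |
| 30 | 0.74 SD | 0.85 SD |

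The normal approximation, (z_α + z_β) × √(2/n), gives 0.81 and 0.94 SD at 24 per arm, and 0.72 and 0.84 SD at 30. The difference does not matter here.

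**3. If several PPSG parameters are tested with multiplicity control.** With Bonferroni over three, each at 0.05 / 3 = 0.0167, the detectable effect at 90% power rises to about 1.10 SD with 24 per arm and 0.97 SD with 30.

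**4. Power over a range of assumed effects** (two-sided 0.05, noncentral t; the effects are assumptions, not figures from the protocol):

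| Assumed effect | 24 per arm | 30 per arm |
|---|---|---|
| 0.4 SD | 27% | 33% |
| 0.6 SD | 53% | 63% |
| 0.8 SD | 77% | 86% |
| 1.0 SD | 92% | 97% |

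**5. The ISI itself.** The 0.6 SD row is the ISI assumption: 53% power with 24 per arm and 63% with 30, against the stated 90%. By the t-test, 90% power needs about 60 per arm (59.4 before rounding up).

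**The case against.** Four points can be made on the other side.

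First, α = 0.05 in the Sample size section equals the threshold in the Statistical analysis section, so it does apply to the PPSG tests. This stands: the failure to carry over concerns power only. A reader might infer that neither α nor β has any bearing on the primary outcome, but the documents do not support that for α.

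Second, a reader might infer that the primary test has no power, or has 53% to 63% power. Neither follows. Its power is unstated, and it depends on an effect the article does not give. The 53% to 63% belongs to the ISI. It applies to PPSG only as an illustration, if the PPSG effect were also 0.60 SD. The gap between it and 90% comes from the two-group arithmetic in step 1, not from the choice of outcome.

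Third, the Introduction does not say that ISI and PPSG effects diverge, only that earlier work leaned on scales. The stated aim is to assess PPSG together with sleep scales, so the ISI belongs to the efficacy question. This softens the mismatch but does not remove it: the ISI is still formally secondary, and no link between the two effects is offered.

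Fourth, one might say that a condensed article leaves such detail to the full protocol or analysis plan. Here the article states its sizing basis in full (outcome, SD, effect, α, β, N and drop-out), so the mismatch lies in what is stated and not in what is left out.

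**Conclusion.** The point holds, limited to power. The trial is sized on a secondary outcome, and the stated 90% power does not describe the PPSG primary comparison. What 24 to 30 evaluable patients per arm provide is a detectable effect of 0.96 to 0.85 SD at 90% power, or 0.83 to 0.74 SD at 80%. These figures assume one PPSG parameter, a two-sided unadjusted t-test at 0.05 and equal arms. They grow if several parameters are tested with multiplicity control. Whether such effects are plausible for PPSG cannot be judged from the document.

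A separate fault sits in the same paragraph: the ISI calculation does not deliver 90% power for the ISI in a two-group comparison either. Correcting that arithmetic alone would still leave the primary outcome without a sample-size basis.

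**What to change.** 1. Name one of the PPSG parameters already listed under Primary outcome measures as the primary.
2. In the Sample size section, replace the 90% power statement with the detectable between-group effect for that single test: 0.96 SD (90%) or 0.83 SD (80%) with 24 evaluable per arm, and 0.85 or 0.74 SD with 30. State that these grow if several PPSG parameters are tested with multiplicity control, for example to about 1.10 and 0.97 SD at 90% power with Bonferroni over three.
3. Convert the effect to minutes, percentage points or counts with the blinded pooled baseline SD of the named parameter. Mark the result as approximate, because the SD of post-treatment or change values may differ from the baseline SD and the article does not say which will be compared.
4. Do not leave the ISI calculation as it stands. Label it as concerning a secondary outcome and restate its power for a two-sided two-group test: about 53% with 24 per arm and 63% with 30, with about 60 per arm needed for 90%.

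The cost is wording plus one blinded SD calculation from baseline recordings that the schedule already includes. No more patients are needed. The downside is that the stated sensitivity becomes less favourable.

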**Discussion:**

This study aims to evaluate the efficacy of acupuncture using the portable polysomnography combined with sleep scales, and analyze heart rate variability to preliminarily explore the underlying mechanism of acupuncture on hypertension with insomnia. The trail, if proven to be effective, will provide strong scientific evidence to support acupuncture is effective to manage patients for hypertension with insomnia.

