### Statistical analysis

In this study, all statistical analyses will be conducted by an independent statistician using SPSS 25.0 software (IBM, Armonk, NY, USA). The measured data will be expressed as mean ± standard deviation, and the count data will be expressed by the ratio or composition ratio. For comparing measured data between the two groups, first normal analysis will be performed. A *t*-test will be used for the measured data conforming to normal and homogeneity of variance, and a nonparametric rank sum test will be used for non-normally distributed measured data. The data will be counted by the Chi-Square test or Fisher's exact test. *P* values ≤ 0.05 will be considered statistically significant.

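### The N ≈ 24 used per arm does not give 90% power for a two-arm comparison: on the protocol's own inputs, power is about 53% (63% with all 30 per arm)

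*Protocol article*

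**What the plan says.** The protocol article, under Sample size, states: "The calculation of sample size will be based on the change of ISI scores". The inputs are that "the overall standard deviation of ISI scores in patients of hypertension with insomnia was 5.5, ISI scores decreased by 3.3 after treatment", with "α = 0.05, β = 0.10". From these it reports N ≈ 24. After a 20% allowance for loss it concludes "so there were 30 cases in the treatment group and 30 cases in the control group", 60 in total. It names neither the formula nor whether the test is one- or two-sided.

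The Design section describes 1:1 allocation to acupuncture and sham. The Statistical analysis section, which opens its test description with "For comparing measured data between the two groups", plans a t-test or a rank sum test, with P ≤ 0.05 counted as significant. It mentions no adjustment for baseline.

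**The concern.** Because 24/0.8 = 30, the 24 serves as the number per arm. For a standardised difference of 3.3/5.5 = 0.60 at 90% power, 24 per arm is far too few for two independent groups, since the variance of a difference between two means is twice that of a single mean. The effect is also described as a fall after treatment, which is a within-group change. The contrast that the trial is designed to test is the advantage over sham.

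This is the only power statement in the protocol, and it is the basis for the 60 patients. If it is wrong, the trial would miss the effect it assumes nearly half the time, and a null result could be taken as evidence that acupuncture does not work. The abstract says that a positive result "will provide strong scientific evidence to support acupuncture is effective", and the stated β = 0.10 lends that expectation support it does not have.

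**Working it through.** **Inputs.** From the Sample size section: difference 3.3, SD 5.5, α = 0.05, power 0.90, loss 20%. From Design and Statistical analysis: two parallel arms, 1:1, compared by t-test. Two-sided testing is assumed; one-sided results are shown alongside.

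**1. Reproducing the stated 24.** One-sample (pre-post) formula, one-sided α, normal approximation:

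n = (z₀.₉₅ + z₀.₉₀)² × SD²/δ² = (1.645 + 1.282)² × 5.5²/3.3² = 8.564 × 2.778 = 23.8 → 24.

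Then 24/(1 − 0.20) = 30, which matches the plan. The two-sided version of the same formula gives 10.507 × 2.778 = 29.2 → 30, before any loss.

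**2. What the two-arm comparison needs.** n per arm = 2 × (z_α + z_β)² × SD²/δ²:

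| Test | Normal formula | t-test |
|---|---|---|
| Two-sided 0.05 | 2 × 10.507 × 2.778 = 58.4 → 59 | 60 |
| One-sided 0.05 | 2 × 8.564 × 2.778 = 47.6 → 48 | 49 |

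No two-sample version gives 24 per arm at β = 0.10. With 20% loss, 59 or 60 evaluable per arm becomes 74 or 75 randomised per arm, 148 to 150 in total.

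**3. Power at the planned size** (noncentral t, difference 3.3, SD 5.5):

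| Per arm | Two-sided | One-sided | Stated |
|---|---|---|---|
| 24 evaluable | 53.0% | 65.6% | 90% |
| 30 evaluable | 62.8% | 74.3% | – |

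The normal approximation gives 54.7% and 64.2% two-sided.

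**4. Difference detectable with 90% power, two-sided.**
- 24 per arm: 0.956 SD, and 0.956 × 5.5 = 5.3 points.
- 30 per arm: 0.851 SD, and 0.851 × 5.5 = 4.7 points.

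**5. If the 3.3 is a within-group fall.** The protocol gives no figure for improvement under sham. Assuming 1.0 to 1.5 points, the between-arm difference is 2.3 to 1.8 points, and power at 24 per arm falls to 29% and 20%. This is an illustration only; the main result uses the full 3.3.

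**The case against.** The strongest points on the other side are these.

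- **The origin of 24 is inferred.** This is true: no formula or sidedness is given. Other routes to 24 exist, such as taking the one-sided two-sample 48 per arm as a total for both arms, or a one-sample two-sided t-test at 80% power (which contradicts β = 0.10). The shortfall does not depend on the route. If 24 were meant as a total, 12 per arm would have about 29% power.
- **Sidedness is not stated.** With a one-sided test, power is 66% and 74%. That is better, but still well short of 90%.
- **It is unclear whether 5.5 is the SD of a score or of a change.** This stands as a real uncertainty. If it is a score SD and change is analysed, the SD of change is 5.5 × √(2(1 − r)). At assumed baseline-to-post correlations r of 0.3, 0.5 and 0.7, power at 24 per arm is 41%, 53% and 75%.
- **Baseline adjustment could recover power without more patients.** In part. With a score SD of 5.5 and assumed correlations of 0.5 to 0.7, power at 30 per arm is about 75% to 89%. At 24 per arm, 90% needs an effective SD of about 3.5. The protocol gives no correlation and plans an unadjusted test.
- **ISI is a secondary outcome.** This is correct and limits the scope. These figures say nothing about the primary polysomnography parameters, for which the Sample size section makes no power statement. The restated text should say so.
- **The abstract's claim is conditional on a positive result, and the limitations already call for verification in a larger sample.** This is fair. Rewording the abstract is a matter of judgement and is not part of the error.

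**Conclusion.** The concern holds. The stated inputs do not give 24 per arm for the comparison that the trial makes. Power for a 3.3-point difference in ISI is about 53% with 24 evaluable per arm and 63% with 30, which is 37 and 27 percentage points below the 90% stated. These values assume a two-sided 0.05 t-test, SD 5.5 for the quantity analysed, and 3.3 as the true advantage over sham. One-sided testing or the assumed correlations above move the figures, but none of those variants restores 90% at 24 per arm. The loss inflation from 24 to 30 is arithmetically correct. This must be corrected, because the protocol's only power claim is wrong as written.

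**What to change.** Keep 60 patients and rewrite the Sample size section:

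- Remove the β = 0.10 claim and the statement that 24 follows from it.
- State that the comparison is between arms and two-sided, and that the calculation concerns ISI, a secondary outcome.
- Replace the result with wording such as: with 24 evaluable (30 randomised) per arm, a two-sided t-test at 0.05 has about 53% (63% if all are evaluable) power for a 3.3-point between-arm difference with SD 5.5; the difference detectable with 90% power is 5.3 (4.7) points.
- Say whether 5.5 is the SD of a score or of a change, and whether 3.3 is a within-group fall or a difference from a control.
- State that a non-significant result will be interpreted through its confidence interval and not as absence of effect.

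Calling the trial exploratory and softening the abstract's statement about strength of evidence would fit the restated power, but these are optional.

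The cost is wording only, with no additional patients. The stated power becomes less favourable. Reaching 90% by enlarging the trial would take 148 to 150 patients. The Trial status section reports that randomisation has begun and that recruitment is due to end in late 2022, so correcting the text is the more realistic course.

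### The 24 patients per arm do not follow from the stated inputs: a two-arm, two-sided comparison needs about 60 per arm, and power at 24 and 30 per arm is 53% and 63%, not 90%

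*Protocol article*

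**What the plan says.** The protocol article, Sample size section, sets the basis: "The calculation of sample size will be based on the change of ISI scores". Citing a published source, it says that the overall standard deviation of ISI scores in this population "was 5.5, ISI scores decreased by 3.3 after treatment, α = 0.05, β = 0.10". The result is about 24 cases. A loss of 20% is then allowed for, "so there were 30 cases in the treatment group and 30 cases in the control group", which makes 60 in total. Since 24/(1 − 0.20) = 30, the 24 is used as a per-arm figure.

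The Design section describes 1:1 randomisation to acupuncture or sham acupuncture. The Statistical analysis section specifies a t-test, or a rank sum test if the data are not normal, "For comparing measured data between the two groups". It sets the threshold as P "values ≤ 0.05 will be considered statistically significant". Neither section states whether the test is one-sided or two-sided, and the sample-size formula is not shown.

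**The concern.** The standardised effect is 3.3/5.5 = 0.6. A two-group comparison at that effect with 90% power needs far more than 24 per arm, because the variance of a difference between two means has a contribution from each arm. The printed figure has the size expected when only one group's variance is counted.

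This is the article's only sample-size justification. A reader will take from it that the trial has 90% power for a 3.3-point ISI benefit. If the true figure is little better than one half, a non-significant ISI result would look like good evidence against an effect that the trial was likely to miss.

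There is also an ambiguity about the standard deviation. The calculation is said to rest on the change in ISI, but the 5.5 is described as the standard deviation of ISI scores. The two are equal only if the correlation between baseline and week 4 is exactly 0.5.

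**Working it through.** **Inputs (Sample size section).** SD = 5.5; difference = 3.3; α = 0.05; β = 0.10, so power is 90%; loss 20%. Standardised effect d = 3.3/5.5 = 0.6, d² = 0.36. Normal quantiles: 1.960 (two-sided α), 1.645 (one-sided α), 1.282 (90% power). I take 3.3 as the true acupuncture-versus-sham difference, although the text words it only as a fall after treatment.

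**Step 1: reproduce the printed figure.**
- One group, one-sided: (1.645 + 1.282)²/0.36 = 23.8, so 24. This matches.
- One group, two-sided: (1.960 + 1.282)²/0.36 = 29.2. No match.
- Loss: 24/0.8 = 30. This matches.

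**Step 2: the comparison that the trial will make.** For two equal arms, n per arm = 2(z_α + z_β)²/d².
- Two-sided: 2 × (1.960 + 1.282)²/0.36 = 58.4. With the noncentral t distribution it is 59.4, so 60 per arm.
- One-sided: 2 × (1.645 + 1.282)²/0.36 = 47.6. With the t distribution it is 48.3, so 49 per arm.

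Neither is near 24. Reading 24 as the total, 12 per arm, fits even less well. With the plan's 20% loss, 60 per arm becomes 60/0.8 = 75 per arm.

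**Step 3: power at the planned sizes** (t-test, d = 0.6).

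| Patients per arm | Two-sided power | One-sided power | Difference detectable with 90% power (two-sided) |
|---|---|---|---|
| 24 (after the planned 20% loss) | 53.0% | 65.6% | 5.3 points |
| 30 (no loss) | 62.8% | 74.3% | 4.7 points |

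**Step 4: if 5.5 is the SD of scores and change is analysed.** SD of change = 5.5 × √(2(1 − ρ)), where ρ is the correlation between baseline and week 4. The article gives no ρ, so the values below are assumptions.

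| Assumed ρ | SD of change | Per arm for 90% power (two-sided) | Two-sided power at 24 per arm |
|---|---|---|---|
| 0.3 | 6.51 | about 83 | about 40% |
| 0.5 | 5.50 | about 60 | 53% |
| 0.7 | 4.26 | about 36 | 75% |
| 0.8 | 3.48 | about 25 | 90% |

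For 24 per arm to give 90% power, the SD of change would have to be about 3.45, which means ρ of about 0.80. The article states neither figure.

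**The case against.** The core arithmetic is hard to contest, because the inputs and the result stand in the same paragraph and no two-arm formula links them. Five objections bear on how the point is put.

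- **The formula is inferred.** The article shows no formula. That 23.8 matches a single-group, one-sided calculation is a reconstruction. This stands, but the finding needs only that 24 does not follow for two arms.
- **Sidedness is not stated.** Two-sided testing is a convention here. This stands, so both sets of figures are given. One-sided testing raises power to 66% and 74%, still well short of 90%.
- **The 3.3 may not be a between-arm difference.** It is described as a fall after treatment. The power figures are therefore conditional on granting it as the difference from sham. If it is only a within-group fall, the effect against sham has not been specified at all, which does not rescue the calculation.
- **The SD may be misread.** Whether 5.5 belongs to scores or to change depends on a source not at hand, and with ρ near 0.8 the printed size would be adequate. This is fair: the point is an ambiguity to clear up, not a second arithmetic error. But an unstated correlation near 0.8 cannot be assumed in the plan's favour.
- **ISI is a secondary outcome.** The primary outcome is the set of portable polysomnography parameters, for which the article gives no power statement. The consequence is therefore confined to conclusions about ISI, the outcome on which the trial was sized.

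**Conclusion.** The concern holds. For the two-arm comparison that the article describes, 24 per arm does not follow from an SD of 5.5, a difference of 3.3, α = 0.05 and 90% power. The two-sided requirement is 60 per arm, 2.5 times the printed figure. Power for a 3.3-point difference is 53% at 24 per arm and 63% at 30 (two-sided), or 66% and 74% (one-sided).

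These figures assume that 3.3 is the true difference from sham and that 5.5 is the SD of the quantity compared. If change is analysed and 5.5 is the SD of scores, two-sided power at 24 per arm runs from about 40% to 90% for ρ between 0.3 and 0.8. Only the top of that range reaches the claimed value, and the article does not state the correlation that it requires.

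**What to change.** Keep 30 per arm and correct the Sample size paragraph:

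- Replace the 24 cases and the β of 0.10 with the two-sample, two-sided result. For example: with 24 evaluable patients per arm, a 3.3-point difference and an SD of 5.5, power is about 53%, and the difference detectable with 90% power is about 5.3 points.
- State that the test is two-sided and that 3.3 is taken as the difference from sham.
- Say whether 5.5 is the SD of ISI scores or of their change. If it is the SD of scores, give the assumed correlation between baseline and week 4 and the resulting range of power.
- State in the analysis and discussion that a non-significant ISI result does not rule out a 3.3-point effect.

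The cost is rewording of one paragraph and a sentence on interpretation. No extra patients are needed, so it can be done although randomisation has begun. The stated power becomes less favourable; the correction discloses the shortfall and does not remove it.
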